### Intervention

All participants will complete five daily sessions of tDCS (NeuroConn DC-Stimulator, Neurocare Group, Germany). A 0.9% saline-soaked anodal electrode (5 x 7 cm) will be placed over the ipsilesional M1 (hotspot of the affected first dorsal interosseous muscle, FDI); the cathodal electrode (5 x 7 cm) will be placed over the contralateral supraorbital area. The FDI hotspot will be determined at baseline using standard TMS protocols [46]. Participants in the anodal tDCS group will receive 2 mA stimulation for 20 minutes with a ramp-up and ramp-down time of 30 s at the beginning and end of the stimulation. The sham group will receive 2 mA electrical stimulation for 30 seconds after which the current will be ramped down to zero. This tDCS protocol complies with current safety recommendations and is in line with previous investigations examining the effects of tDCS on pathological fatigue [25,27,31,47]. Participants will remain seated during the stimulation and be instructed to minimize arm movements.

All interventionists will receive standardized training from the principal investigator (PI). A detailed intervention log will be completed at each session. The log includes information about electrode placement, start and end times of stimulation, and any deviations from the protocol. After each tDCS session, the interventionist will document the type and severity of any side effects. The PI will review all intervention logs and discuss protocol deviations and side effects with the interventionists. After the last study assessment (follow-up), participants will be asked whether they believe they were in the anodal or sham group and rate their level of confidence in their group assignment (scale from 1 to 10) [48].

All participants will be asked to adhere to their regular medications and therapies unless they will instructed otherwise by their care providers. Any changes in their care plans will be documented.

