### Randomization and blinding

Eligible participants will be randomized into either the anodal or sham tDCS group using a blocked randomization procedure. The blocked randomization will create groups that have equal numbers of females because sex is a determinant of PSF [44,45]. The study biostatistician who is not involved in intervention or assessments will assign the participants and prepare concealed envelopes with group allocation. The concealed envelopes will be given to the interventionists who will provide tDCS intervention but will not participate in the assessments. Participants and outcome assessors will be blinded to group assignment.

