### Assessments and outcomes

All participants will take part in clinical, behavioral, and neurophysiological assessments at baseline, post-intervention, and one-month follow-up. All assessors will be blinded to group assignment and trained by the PI prior to study commencement. A detailed manual of procedure has been developed to outline all assessment procedures.

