### Ethics and monitoring

Ethical approval has been obtained from the Texas Woman’s University Institutional Review Board (FY2023−226). The PI will obtain the informed consent and all participants will provide written informed consent. An independent Data Monitor and Safety (DMS) officer will review study progress, protocol deviations, and adverse events on a quarterly basis. Adverse events will be documented and reviewed by the investigators quarterly. Serious adverse events will be reviewed immediately and reported to the IRB and DMS officer. Protocol amendments will be reported to the DMS officer, IRB and funding agency. Interim analysis is not planned for this trial. In the events of serious adverse events, participant’s group assignment will be unblinded.

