## Discussion

This study will address a long-standing problem in stroke recovery, PSF, with a novel and evidence-based intervention, tDCS, and a robust double-blind randomized controlled design. Our rich dataset composed of clinical, behavioral, neurophysiological and neuroimaging data will assist in a thorough evaluation of the effects of tDCS on PSF.

PSF is a complex, multifactorial phenomenon and likely require a multimodal approach for effective management. We propose to use neuromodulation based on the association between PSF and altered brain excitability and connectivity. Modulating brain excitability via non-invasive brain stimulation not only offers an alternative to pharmacological approaches but also provides a more targeted intervention. Previously examined strategies that have been found to be effective in reducing PSF include graded physical activity [59], cognitive-behavioral training [60], and central acting pharmacological agents [61]. These strategies share a common feature, inducing neuroplasticity. Compared to non-invasive brain stimulation, these strategies are less targeted which may contribute to variability in responses. Non-invasive brain stimulation, such as tDCS, is effective in promoting motor recovery after stroke [32] and holds promise as a treatment of non-motor symptoms such as PSF. In the current study, we choose tDCS as the non-invasive brain stimulation tool because it is safe, tolerable, and produces minor transient side effects compared to other non-invasive brain stimulation techniques such as repetitive TMS, making it a promising tool to be integrated into clinical practice.

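### Side effects are documented and graded by interventionists who receive the allocation, so any by-arm summary of them would be open to observer bias (minor, safety data only)

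*Protocol article*

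**What the plan says.** Three parts of the protocol article bear on this.

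- **Allocation.** Under Randomization and blinding, the biostatistician is to "prepare concealed envelopes with group allocation". The section continues: "The concealed envelopes will be given to the interventionists who will provide tDCS intervention but will not participate in the assessments". It then states who is blinded: "Participants and outcome assessors will be blinded to group assignment". Interventionists are not on that list.
- **Side effects.** Under Intervention: "After each tDCS session, the interventionist will document the type and severity of any side effects". The next step is a review with the same staff: "The PI will review all intervention logs and discuss protocol deviations and side effects with the interventionists".
- **Assessments and safety review.** Under Assessments and outcomes: "All assessors will be blinded to group assignment and trained by the PI prior to study commencement". That section covers the clinical, behavioral and neurophysiological assessments at baseline, post-intervention and one month. Under Ethics and monitoring: "Adverse events will be documented and reviewed by the investigators quarterly". An independent safety officer also reviews adverse events each quarter. The article does not say whether either review is blinded.

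**The concern.** A severity grade involves judgement, and what gets recorded as a side effect depends partly on how the participant is asked. When the person asking and writing knows the arm, both can drift with expectation. More may be sought or graded higher under active current, or complaints may be played down because they are expected and familiar. The direction cannot be predicted.

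The article accepts this principle for its outcomes by keeping interventionists out of the assessments. The per-session side-effect record falls outside that protection.

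What is at stake is the credibility of any anodal-versus-sham summary of harms. The article says that the trial will be reported under CONSORT and that its results will inform clinical treatment, so readers are likely to look for such a summary.

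**Working it through.** The point concerns procedure, and the article gives no figure for side effects to reproduce. The check sets the passages side by side and then shows the arithmetic for scale.

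**1. Do the interventionists know the arm?** They receive envelopes containing the allocation. They deliver either 20 minutes of 2 mA or a current that is ramped down after 30 seconds. They are missing from the list of blinded roles. The article does not state outright that they know the arm, but no other reading fits well.

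**2. Do the same people record side effects?** Yes. The Intervention section assigns type and severity to the interventionist after each session.

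**3. Does assessor blinding cover that record?** No. It applies to the three scheduled assessment points, whereas the side-effect record is made at each of five treatment sessions by staff who take no part in the assessments.

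**4. Does a later step repair it?** None is described. The principal investigator discusses side effects with the same interventionists, and no blinded adjudication is stated for the quarterly reviews. Whether those reviews draw on the session logs is likely but not stated.

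**5. Does a planned analysis use the record?** No. Side effects are not among the primary, secondary or exploratory outcomes. The group-by-time analyses under Data management and data analysis cover clinical, behavioral and neurophysiological outcomes and do not name side effects.

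**6. Scale.** Inputs: 16 per group (Sample size estimation) and five sessions each (Intervention).

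- Side-effect records: 32 × 5 = 160 in all, 16 × 5 = 80 per arm.
- Weight of one participant in one arm: 1/16 = 6.25 percentage points.
- Two participants recorded differently: 2/16 = 12.5 points. Three: 3/16 = 18.75 points.
- Read the other way, an assumed shift of 10 to 20 points is 0.10 × 16 = 1.6 to 0.20 × 16 = 3.2 participants. For example, equal true counts could be recorded as 8 versus 11.

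The 10 to 20 point range is purely illustrative and has no source in the article. It shows only that a handful of differently worded questions would be visible in a trial of this size.

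**The case against.** Much of the case on the other side stands.

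- **No tolerability comparison is planned.** A reader might infer that the trial's tolerability comparison is made unblinded. The article names no such comparison, and side effects appear only as session logging and safety monitoring. The point is therefore conditional on a by-arm summary being made.
- **The double-blind label is not contradicted.** A reader might infer that unblinded recording makes the label wrong. The article says who is blinded and openly places interventionists outside both the blind and the assessments.
- **The interventionist may be transcribing.** Documenting severity does not exclude writing down what a blinded participant reports, perhaps on a standard form. The article mentions standardized training and a detailed log, and an article may leave the form itself to the full protocol. Any bias could thus be partial. It would not disappear, because the prompting and the writing still rest with allocation-aware staff.
- **The tolerability statement is background.** The Discussion says of tDCS that "it is safe, tolerable, and produces minor transient side effects", in comparison with other stimulation techniques such as repetitive TMS. An anodal-versus-sham table could not test that claim, so the statement does not make tolerability an endpoint.
- **Cueing of participants is speculative.** One might argue that arm-dependent questioning could reveal the allocation and so affect the self-reported FSS. Nothing in the article shows this. The interventionist is present at all five sessions whoever fills in the form, and the participants' guess of their group, with a confidence rating, is collected after follow-up.
- **Safety oversight exists.** Serious events are reviewed immediately and reported to the IRB and the independent officer. That protects participants, but it does not make the session records blinded.

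**Conclusion.** The point holds in a limited form. As described, side effects and their severity are recorded by staff who receive the allocation, with no participant-completed or blinded collection stated. Any by-arm summary of side effects would be open to observer bias of unknown direction and size, at 6.25 percentage points of one arm per participant affected.

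This rests on two assumptions: that interventionists know the arm, which is a strong inference, and that someone will summarise side effects by arm, which is likely under CONSORT reporting but not stated.

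The primary FSS and input-output curve results are not collected through this log, and no planned test depends on it. It is a minor point on safety data, not a failure of the blinding of outcomes.

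**What to change.** For the remaining sessions:

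1. After each session, have the blinded participant complete a fixed side-effect checklist with a severity score, using the same items and wording in both arms, before the interventionist comments on it.
2. Use that form for any by-arm harms summary.
3. Keep the interventionist's log for device data, protocol deviations and events needing action.
4. Report sessions already completed separately, stating that side effects were recorded by allocation-aware staff. Do not pool the two methods.

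The cost is one short form and about a minute per session, plus a small protocol wording change, with no extra staff or visits. The drawback is two collection methods within one trial. Recruitment began in December 2023 and is due to finish in May 2026, so the new form can cover only part of the 160 sessions, and a by-arm summary from it would rest on fewer than 16 participants per group. If too few sessions remain to justify the form, the minimum is to state in the trial report who recorded side effects and that they held the allocation.

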### Assessments and outcomes

All participants will take part in clinical, behavioral, and neurophysiological assessments at baseline, post-intervention, and one-month follow-up. All assessors will be blinded to group assignment and trained by the PI prior to study commencement. A detailed manual of procedure has been developed to outline all assessment procedures.

#### Clinical and behavioral assessments and outcomes.

The primary outcome for fatigue will be the Fatigue Severity Scale (FSS) score. FSS is a self-report questionnaire measuring the severity and impact of fatigue [41]. The FSS contains nine items rated on a 7-point Likert scale (1 = strongly disagree and 7 = strongly agree). The total score ranges from 9 to 63 with a higher score indicating greater fatigue. The FSS has been validated in chronic stroke [49]. Secondary measures of fatigue will be the Fatigue Scale of Motor and Cognitive Functions (FSMC) and Visual Analog Scale-Fatigue (VAS-F). The FSMC is a self-report questionnaire developed to measure cognitive and motor fatigue separately [50] and has been validated in chronic stroke [51]. The FSMC contains 20 items (10 for cognitive fatigue and 10 for motor fatigue) rated on a 5-point Likert scale. The total score ranges from 20 to 100 with a higher score indicating greater fatigue. The Visual Analog Scale-Fatigue (VAS-F) is a numerical scale ranging from 1-10 with a higher value indicating a higher level of global fatigue [52].

We previously showed that individuals with PSF reported high perceived effort during reaching and exhibited poor reach performance [16]. In the current study, we will adopt the same reaching task to evaluate changes in perceived effort and reach performance as a secondary measure of fatigue. At each assessment time point, participants will perform goal-directed reaches as fast and accurately as possible toward four targets that vary in distance and direction on a digitized tablet in sitting. Participants will also reach toward two central targets at both self-selected and fast speeds (i.e., as fast as possible) to evaluate the discrepancy between their movement choice (self-selected) and their capability (fast) [16]. Borg Rating of Perceived Exertion (Borg RPE) [53] and Paas Mental Effort Rating Scale (Paas MERS) [50] will be used to quantify perceived physical and mental effort associated with reaching, respectively. Borg RPE ranges from 6–20, with a higher value indicating greater perceived physical exertion. Paas MERS is a 9-point Likert scale that ranges from 1 (very, very low mental effort) to 9 (very, very high mental effort).

#### Neurophysiological assessments and outcomes.

A TMS device (The Magstim Company Ltd, Whitland, UK) will be used to quantify changes in cortical excitability. Surface electromyography electrodes will be placed on the affected FDI and triceps muscles while participants are seated. Each participant’s structural brain MRI will be used to guide TMS coil placement using the Brainsight Neuronagivation system (Rogue Research, Canada). For each muscle, the following TMS outcomes will be derived: resting motor threshold (RMT), motor evoke potential (MEP) amplitude, input-output curve, short-interval intracortical inhibition (SICI), and intracortical facilitation (ICF).

RMT is the minimum stimulus intensity to elicit an MEP ≥ 50 µV in amplitude in at least 3 of 5 consecutive stimulations. MEP will be elicited at rest with a stimulus intensity at 120% of RMT and at 100% maximal stimulation output. The averaged peak-to-peak MEP amplitude will be calculated to index corticospinal excitability. We will also construct an input-output curve using six stimulation intensities (100–150% of RMT) to assess corticospinal excitability and motor recruitment. Both intracortical inhibition (SICI) and facilitation (ICF) of M1 will be measured with the conditioning stimulus set at 80% RMT and the test stimulus intensity set at 120% RMT. SICI will be elicited at an inter-stimulus interval of 2 ms whereas ICF will be elicited at an inter-stimulus-interval of 15 ms. The primary measure of brain neurophysiology will be the input-output curve slope obtained from the FDI with a steeper slope indicating greater excitability [54]; all other TMS measures will serve as exploratory outcomes.

The secondary measure of brain neurophysiology will be functional connectivity of the fronto-striato-thalamic network. Participants will undergo a brain MRI on a 3T Siemens scanner with a 32-channel head coil at baseline and post-intervention. High-resolution T1- and T2-weighted anatomical scans and 10 minutes of resting state functional MRI will be acquired. Data will be preprocessed (spatial distortion correction, realignment, coregistration, normalization, smoothing, detrending, removal of lesion artifacts) using a pipeline tuned for the stroke damaged brain [55]. The mean BOLD signal between brain regions will be correlated over time resulting in a first-level connectivity matrix for each participant. Pairwise correlations between the regions of interest (M1, dorsolateral prefrontal cortex, striatum, thalamus) in the fronto-striato-thalamic network will be extracted for each participant. A higher correlation coefficient indicates greater connectivity. Functional connectivity of other networks, such as sensorimotor network [19], fronto-parietal network [38], and the default mode network [56] will be explored to further examine the neurophysiological effects of tDCS on PSF.

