Studies have suggested that PSF involves neural networks beyond M1 [20–22]. A pharmacological trial showed that functional connectivity of the fronto-striato-thalamic network predicted Modafinil induced PSF reduction [34]. Fronto-striato-thalamic network has been implicated in other pathological fatigue [35–37] and is likely to play a role in PSF [38]. Further, because the fronto-striato-thalamic network is anatomically and functionally connected to M1, altered M1 excitability after stroke is likely related to connectivity in this network [39,40]. Therefore, tDCS applied to M1, in addition to changing M1 excitability, might also modulate the fronto-striato-thalamic network and result in reduced PSF. Examining both brain excitability and connectivity might shed light on the underlying mechanism of PSF and the working mechanism of tDCS on PSF.

The purpose of this double-blind, randomized controlled trial is to investigate the effects of multiple sessions of anodal tDCS to ipsilesional M1 on PSF and underlying neurophysiology. We hypothesize that compared to the sham group, the anodal tDCS group will show a greater decrease in fatigue and the effect will last up to 1 month (Aim 1). We also hypothesize that compared to sham tDCS, anodal tDCS will significantly increase ipsilesional M1 excitability and the functional connectivity between ipsilesional M1 and the fronto-striato-thalamic network (Aim 2). Lastly, we hypothesize that individuals who show a greater change in the neurophysiological outcomes (M1 excitability, brain connectivity) will demonstrate a greater reduction in fatigue (Aim 3).

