### Sample size estimation

Previous tDCS studies on pathological fatigue reported medium-large effect sizes (f > 0.35) [25,27,57,58]. A *prior* power analysis (G*Power version 3.1.9) using a more conservative effect size (f = 0.25), a power of 0.80, α-level at 0.05, and a correlation among the repeated measures of 0.5 indicate that a minimum of 28 participants is required for repeated measures analysis of variance (ANOVA). With consideration of a 10% attrition rate, a sample size of 32 (N = 16 per group) will be required.

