### Data management and data analysis

Clinical and behavioral data will be collected via paper-based questionnaires and entered into the online Research Electronic Data Capture (REDCap) hosted at the Texas Woman’s University. All paper-based files will be coded and stored in a locked cabinet with files consisting of identifiable information (e.g. informed consent) kept separate from the clinical data. Kinematic data and neurophysiological data will be in electronic format. All electronic data will be stored on password-protected university servers. All data will be coded to ensure participant confidentiality throughout the study. The statistician and the principal investigator will review the data every three months to ensure completeness and data quality. The final de-identified dataset will be deposited to NICHD DASH for public access upon the completion of publications.

All data analyses will be performed in SPSS v28 (SPSS Inc., IBM, USA) by the biostatistician and significance will be set at p < .05. The percentages and patterns of missing data will be assessed to determine if pairwise deletion will be used for analysis or if an intention-to-treat strategy needs to be applied to replace missing values [57]. Comparison of baseline variables between groups will be conducted. If a baseline difference exists and judged to be a potential confound (e.g. baseline FSS score), the variable will be included as covariate in the primary analyses. Normality and outliers will then be checked to see if parametric analysis assumptions are met.

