To examine effects on clinical, behavioral, and neurophysiological outcomes, we will perform a 2 group (anodal, sham) x 3 time point (baseline, post-intervention, follow-up) repeated measure ANOVA/ANCOVA. Resting state functional MRI data will be analyzed with a 2 group x 2 time point (baseline, post-intervention) ANOVA/ANCOVA. Post-hoc Bonferroni-adjusted comparisons will be completed if a main effect or interaction is detected. To examine whether individuals who show a greater change in neurophysiological outcomes demonstrate a greater reduction in PSF, Pearson or Spearman correlational analyses will be run to examine the relationship between changes in neurophysiological measures (input-output curve, fronto-striato-thalamic network connectivity) and changes in PSF (FSS). The strength of relationships will be interpreted as follows: r < 0.25 = little or no relationship; r of 0.25 to 0.5 = fair; r of 0.5 to 0.75 = moderate; and r > 0.7 = strong relationship [58].

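### The secondary connectivity outcome is defined inconsistently: Aim 2 concerns ipsilesional M1's links, but six region pairs are extracted, three without M1, and then treated as one value

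*Protocol article*

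**What the plan says.** Three sections of the protocol article describe this outcome.

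- **Introduction.** The Aim 2 hypothesis is that anodal stimulation raises M1 excitability and also "the functional connectivity between ipsilesional M1 and the fronto-striato-thalamic network (Aim 2").
- **Neurophysiological assessments and outcomes.** One measure is named: "The secondary measure of brain neurophysiology will be functional connectivity of the fronto-striato-thalamic network". It is made operational as follows: "Pairwise correlations between the regions of interest (M1, dorsolateral prefrontal cortex, striatum, thalamus) in the fronto-striato-thalamic network will be extracted for each participant". No side is given for any region. Other networks are kept apart as things to explore.
- **Data management and data analysis.** The model is given as "Resting state functional MRI data will be analyzed with a 2 group x 2 time point (baseline, post-intervention) ANOVA/ANCOVA", and for all analyses "significance will be set at p < .05". The only multiplicity step is "Post-hoc Bonferroni-adjusted comparisons will be completed if a main effect or interaction is detected". For Aim 3 the planned correlations are between "changes in neurophysiological measures (input-output curve, fronto-striato-thalamic network connectivity) and changes in PSF (FSS").

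**The concern.** The hypothesis, the measurement and the analysis do not describe the same quantity. The hypothesis is about links between one region, ipsilesional M1, and the rest of the network. The measurement is every pair among four regions, so half of the extracted values do not involve M1. The analysis has no factor for region pair and no rule for reducing several values to one, yet it speaks of network connectivity as a single variable.

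This leaves open, after the data are seen, which value stands for the secondary outcome. This outcome carries the connectivity half of Aim 2 and is one of the two neurophysiological variables in Aim 3. The Discussion also relies on it to explain how stimulation works. A change confined to, say, the prefrontal–thalamic pair could be presented as support for an M1 hypothesis that it does not test.

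**Working it through.** **1. Counting the pairs.** Inputs: the four regions named under Neurophysiological assessments and outcomes, each counted once. Pairs = 4 × 3 / 2 = 6.

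- With M1 (3): M1–DLPFC, M1–striatum, M1–thalamus.
- Without M1 (3): DLPFC–striatum, DLPFC–thalamus, striatum–thalamus.

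Only the first three match Aim 2 as worded, and only if they are taken on the lesioned side.

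**2. The three descriptions side by side.**

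| Section | Quantity described | Number of values |
|---|---|---|
| Introduction, Aim 2 | Ipsilesional M1 with the network | 3 pairs, or one summary of them |
| Neurophysiological assessments and outcomes | All pairs of four regions, side not given | 6 |
| Data management and data analysis, Aim 3 | Network connectivity as one variable | 1 |

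**3. Does the stated Bonferroni step cover the pairs?** As written, it starts once an effect has been detected and adjusts the comparisons that follow. Nothing in it adjusts the initial test across region pairs.

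**4. Error rate if each pair has its own test at 0.05.** For k independent tests the chance of at least one false positive is 1 − 0.95^k.

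- k = 6: 1 − 0.7351 = 0.265
- k = 3: 1 − 0.8574 = 0.143

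Pairs that share a region are unlikely to be independent, so these are upper values. A simulation gives the range under correlation: 20,000 runs, 14 per arm, a two-sided t test on each pair's change, and equal correlation between pairs. The correlations are assumed, because the article gives none.

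| Assumed correlation between pairs | Six pairs | Three M1 pairs |
|---|---|---|
| 0 | 0.268 | 0.143 |
| 0.3 | 0.243 | 0.138 |
| 0.5 | 0.209 | 0.127 |
| 0.7 | 0.169 | 0.111 |

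One pre-specified summary tested once has an error rate of 0.05.

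**5. The plan's sample size, and the power left after an adjustment.** Sample size estimation is based on "using a more conservative effect size (f = 0.25), a power of 0.80, α-level at 0.05", with correlation 0.5 among repeated measures. For the group-by-time interaction with m time points, λ = f²·N·m/(1 − ρ), with (m − 1) and (N − 2)(m − 1) degrees of freedom.

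- m = 3, N = 28: λ = 0.0625 × 28 × 3 / 0.5 = 10.5, power 0.812. The stated 28 reproduces, and 28 / 0.9 = 31.1 rounds up to the stated 32.
- m = 2 (imaging), N = 32: λ = 0.0625 × 32 × 2 / 0.5 = 8. Power is 0.78 at 0.05, 0.62 at 0.05/3 = 0.0167 and 0.51 at 0.05/6 = 0.0083.
- m = 2, N = 28: λ = 7. Power is 0.72, 0.54 and 0.43 at the same three levels.

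Applying f = 0.25 and ρ = 0.5 to connectivity is an assumption. The comparison shows that the number of pairs in the confirmatory family matters for power as well as for error.

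**The case against.** The strongest reply is that this is a condensed article about a secondary outcome. How region pairs are summarised, and any adjustment across them, would normally sit in an analysis plan that is not shown. The text says that the correlations are extracted, not that each is tested, and its singular wording is compatible with one summary value. All of that is fair. The absence of a multiplicity rule across pairs is therefore not the point made here.

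What remains is a mismatch between statements that are in the article. The article does settle outcome hierarchy at this level of detail: for TMS it selects the input-output slope from one hand muscle and makes every other TMS measure exploratory, and it sets other networks apart. The three pairs without M1 receive no such label and sit inside the named secondary outcome. A multiplicity rule elsewhere would not by itself reconcile the three descriptions.

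It can also be said that pairs within the network bear on the mechanism, since the Introduction suggests that stimulating M1 may modulate the wider network. That is a good reason to report them, but it does not make them tests of Aim 2 as worded.

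A reader might infer more than the article supports:

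- **That each pair is certainly tested at 0.05.** This is the most natural reading of a model with only group and time as factors, but it is not stated.
- **That untransformed correlations are analysed.** The article says only that a higher coefficient means greater connectivity. It neither states nor excludes a transformation.
- **That all six pairs enter Aim 3.** The text lists network connectivity there as one measure.
- **That both hemispheres are used, giving many more pairs.** No laterality is given in the measurement text, and Aim 2 specifies the ipsilesional side for M1.

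**Conclusion.** The concern holds as an inconsistency of definition. Aim 2 specifies ipsilesional M1's links with the network, the measurement text specifies six pairs of which three exclude M1, and the analysis text treats the result as one variable. The pair count needs no assumption beyond taking each named region once.

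The error rates depend on the reading that every pair is tested separately at 0.05. On that reading the chance of at least one false positive is at most 26.5% under independence, and about 17–24% for assumed correlations of 0.7–0.3. Even the low end is more than three times 5%. If one summary is intended, the error rate is not inflated, but the article does not say which summary, and one built from all six pairs would still not match Aim 2.

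The FSS outcome, the input-output slope and the stated sample size are not affected. The point should be settled before the data are unblinded.

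**What to change.** Bring the three sections to one definition:

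1. Define the secondary connectivity outcome as the ipsilesional M1–DLPFC, M1–striatum and M1–thalamus connectivity, stating the side for each region.
2. Choose in advance between one summary (for example the mean Fisher-z of the three pairs, tested once at 0.05) and three separate tests with Holm adjustment. Either is acceptable.
3. Compare the arms post-intervention with the baseline value as covariate in every case, rather than only if a baseline imbalance is found.
4. Use the same definition in the Aim 3 correlation.
5. Label the three pairs without M1 exploratory. The other networks already are.

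The cost is wording: scans, visits and the processing pipeline do not change. The summary loses sensitivity if only one of the three pairs responds. The Holm option keeps the pairs separate, but its first step is at 0.0167, where power under the plan's own assumptions is about 0.62 with 32 participants, against 0.78 for a single test at 0.05 with the same effect size. Both power figures are for the 2 × 2 interaction, not the covariate-adjusted comparison.
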